## 2. Method

### 2.1. SAGE Overview and Design

SAGE uses a garden-based curriculum to increase physical activity and improve fruit and vegetable consumption in young children, age 3-to-5 years old, at 24 ECECs to help meet national policy guidelines for ECECs [35]. As previously described, SAGE follows the EMO framework and is implemented in ECECs focusing on *micro-level* environmental changes by installing a garden and working with center directors to guide evidence-based ECEC policy choices. At the *meso level*, teacher training and support is used to deliver an enhanced garden-based curriculum to meet *macro-level* ECEC standards for obesity prevention and early education. Parents are engaged using weekly newsletters linked to garden and classroom activities to enhance *exo-level* transfer of benefits [33].

SAGE includes active learning games and songs that use the plant life cycle as a metaphor for human development. Children and teachers complete garden maintenance and exploration time as a part of the curriculum and to promote garden sustainability. Other curricular activities include three science experiments, mindful eating exercises (“tummy mindfulness”) to sample new fruits and vegetables, and interactive discussion time to reinforce content. All activities are designed to align with National Association for the Education of Young Children (NAEYC) teaching standards.

Garden locations are selected with ECEC directors, maintenance staff, and teachers involved with the delivery of SAGE. If a garden exists already but is not used, efforts are made to breathe new life into the existing build or, if it is not well sited (e.g., inadequate or excessive sun exposure, inadequate drainage), to relocate it. SAGE gardens are sized to maximize access for young children (4’ × 6’) and built using inexpensive, and widely available materials (cinderblocks, soil, trellises). CAB members, teachers, and SAGE staff work together to build the garden. Planting seeds and seedlings is incorporated into the curriculum so that children can participate in this activity. See the garden build protocol in Supplementary File S1.

Following the Childhood Obesity Research Demonstration Project (CORD) sustainability model SAGE’s participatory approach was used to develop the SAP to (1) enhance the potential for SAGE to be *replicable*—repeatable, adaptable or expandable, (2) improve the ongoing *continuation of* SAGE *benefits* from program effectiveness, (3) understand existing policy and organizational structures in order to enhance *institutionalization*, and (4) leverage and expand *community capacity* [2]. SAP processes occur before and during implementation, and the impact of the SAP is evaluated throughout the protocol using a mixed methods approach.

### 2.2. Sustainability Action Plan (SAP) Strategies

The SAP incorporates strategies that encourage community members, ECEC teachers, ECEC directors, and parents to engage with SAGE to help create buy-in, improve program delivery, and develop sustainable processes that improve the ability of the ECEC to maintain SAGE. Strategies were developed to engage each stakeholder group (Figure 1). Processes were created on build and maintain the garden, engage all groups and foster coordination, collaboration, and cooperation between them, to enhance behavioral persistence [37], and in turn, sustainability [2].

*Community Advisory Board Meetings.* The SAGE CAB membership, roles, and responsibilities have been previously described [34,35]. In the context of sustainability, the CAB serves as an important resource and sounding board for SAGE. The SAGE CAB for the SAP comprises local community leaders who represent gardening, early childcare, local and state government, and health communities. The CAB and the scientific team identify and implement short-term and long-term goals for the SAP in bi-monthly meetings. CAB members are paid a modest honorarium of $100 annually, and the chair, $200. The CAB provides important information about community capacity and serves as a bridge between the scientific team and community. Each CAB member serves a one-year term at the end of which, the member is given the opportunity to rotate off or continue for an additional term.

*Adaptive Curriculum Delivery Approach.* The SAGE curriculum will be introduced using a continuous one-hour format two times per week for 12 weeks. However, activities may be completed sequentially or re-ordered, offered all in one go, or throughout the school day to fit different teaching styles and classroom schedules. Moreover, activities may be offered indoors or outdoors to accommodate bad weather (e.g., excessive heat).

*Teacher Training and Technical Support.* Another part of curriculum delivery that promotes sustainability is the use of a “see one, do one, teach one” teacher training method that has been used in health care delivery. The first 12 sessions will be led by the research team over six weeks, with teachers observing and assisting in SAGE delivery. Gradually, teachers will begin to lead portions of sessions during this time. Then, the 12 sessions can be repeated over a second six-week period and led by the teachers with assistance from the research team. Teachers will complete a 90-min training session prior to beginning implementation and a 30-min booster session about five weeks into implementation. Trainings focus on five PRIME principles that reinforce best practices for delivering SAGE: *P*romote positive experiences, *R*oom management, *I*mprovement directed reinforcement, *M*odeling appropriate behaviors, and *E*stablishing garden maintenance. On-demand technical support will be available throughout the study for ECECs and teachers who desire additional help.

*Action Planning Meetings with Directors.* Over the course of the SAGE program, research staff will meet three times for one hour with ECEC directors to develop a plan for institutionalizing SAGE and sustaining it beyond the funding period. ECEC directors will also complete assessments to evaluate resources, barriers, and facilitators for sustaining SAGE. In the first meeting, directors will complete a self-assessment of their ECEC, be given the opportunity to ask questions or voice concerns about SAGE, and prompted to think about long-term sustainability. In the second meeting, after they have more experience with SAGE, directors will review the results from their assessments, discuss how their results compare to other ECECs, and develop an action plan and set goals for improving low-scoring areas. Each action plan will be discussed with the CAB to identify community resources to support each ECEC director’s goals and provide feedback. In the final meeting of the semester, SAGE staff and directors will discuss progress towards achieving their goals, reevaluate and set new goals as needed, and complete assessments a second time.

*Newsletters.* SAGE newsletters are designed to engage parents with the curricula, reinforce curricula content when children are at home, and promote the benefits of the ECEC having a garden to encourage parents to become advocates for SAGE. Twelve newsletters are sent out bi-weekly and are coordinated with the SAGE session that children completed during that week. Newsletters include healthy recipes that parents can prepare at home, physical activities for parents and children to complete together, information about local community events for nutrition and physical activity, fun activities for children to complete (e.g., pictures to color, connect the dots drawings), and pictures of children participating in SAGE at the ECEC. Newsletters are available in English and Spanish [33,36].

*Website.* The SAGE website includes information for directors, teachers, and parents about the curriculum, needed materials, and instructions. Links are provided to videos demonstrating active games, science experiments and the tummy mindfulness exercise (https://sites.google.com/asu.edu/sageasu/home, accessed on 1 April 2022). Periodic blog posts provide additional information about school gardening, ideas for engaging kids and families in physical activities, and simple strategies for eating more fruits and vegetables.

### 2.3. SAP Rollout Process

The SAP commences before the curriculum begins and unfolds in a five-step process, which is also described using the plant life cycle as a metaphor. Figure 2 depicts this process and is color coded by stakeholder. Step 1 focuses on planting the idea of sustainability. Steps 2 and 3 focus on reinforcing and growing interest in the concept of sustainability. Steps 4 and 5 empower ECEC staff to sustain SAGE and transition responsibilities and resources associated with SAGE to the ECEC and community.

*SAP Step 1*. *Planting the seeds: Organizational assessment and training (Pre-Implementation).* Prior to implementation, SAGE staff will meet with teachers and ECEC directors to deliver curriculum supplies and conduct an initial training. This training introduces the PRIME principles (described above), provides a brief overview of the curriculum, and gives the ECEC staff a tour of the garden where they have an opportunity to plant seeds as part of the garden introduction. Fresh fruits and vegetables that represent what might be served as part of the curriculum are sampled during this meeting, and several songs and games demonstrated and played with center staff. During all activities, SAGE staff emphasize how the curriculum can fit within current teaching practices and connect activities to NAEYC standards.

*SAP Step 2. Weed control: Identification of challenges (weeks 1–3).* Once ECEC personnel begin to have some experience implementing SAGE, an assessment will be administered to ECEC directors to investigate process factors associated with implementing the new program. Teachers also complete a self-evaluation. Data from all assessments will be reviewed and used to develop the booster training session in SAP Step 3.

*Step 3. Nurturing the seedlings: Overcoming challenges (weeks 4–5)*. Challenges identified in the assessments will be presented to the CAB, ECEC directors and teachers, and the scientific team to allow all parties to develop a shared vision of how SAGE might be replicated in future classrooms. This step also nurtures community capacity by improving evidence-based knowledge about meeting health behavior guidelines and education standards, improves the potential for continuation of benefits to children as they develop, and identifies current and future resources and changes needed to promote institutionalization of SAGE.

At this step, a booster training session will be conducted with teachers. The booster training is used to provide formalized technical assistance as teachers begin to become the primary implementers—switching from the “see one” phase to the “do one” phase of implementation. The booster training helps teachers consider the best processes to integrate SAGE within their teaching styles and existing curriculum. Reflective listening and brainstorming will be used to generate site- and teacher-specific modifications that might be needed for sustainable delivery of SAGE. Booster sessions will be informal, but generally structured around the sustainability of three pieces of the program: gardens, the tummy mindfulness and experiential eating taste tests, and the curriculum.

*SAP Step 4. Preparing for harvest: SAP implementation (weeks 5–10).* Representatives (director, staff, and teachers) from each ECEC will meet with the research team to review how their center fared on assessments. Weaknesses can be identified with strategies to overcome them, based on realistically considering timelines and priorities. Two or three goals will be set based on areas identified for improvement (e.g., improving center policies, sustaining funding, training staff). SAP implementation progress will be reviewed during CAB meetings, and the CAB suggests helpful community resources. The research team will communicate this information and connect ECEC staff to resources.

At the end of step 4 and the 12-week intervention, assessments will be collected to determine how the SAP affects outcomes. Information collected during this phase will be relayed back to the CAB and ECEC directors. The CAB, ECEC directors, and the scientific team will work together to modify SAGE curricular components and implementation protocols for subsequent cohorts of ECECs that receive the SAGE program.

*Step 5. Harvesting the fruit: Interpreting and disseminating findings*. The SAP rollout process continues for three cohorts, including data collection throughout. Information gleaned can inform changes to the SAP. By using a cross-over design, the organizational assessment, development, implementation, and evaluation of the SAP is repeated 6 times over 3 cohorts. Thus, there is the opportunity to develop a comprehensive and robust SAP if changes are needed.

### 2.4. SAGE SAP Sources of Data

To evaluate the impact of the strategies on each CORD construct and at each level of the EMO, a battery of measures designed to include perspectives and reflect priorities of each stakeholder will be administered. A summary, organized by sustainability construct, is presented in Table 1. At the micro level, teacher exit interviews and ECEC directors surveys are conducted, along with on-site environmental surveys (NAP SACC, PARA), and which are to be triangulated with extensive field notes during implementation. The Wilder Collaboration Factors Inventory is completed annually with our community advisory board. At the meso-level, in addition to relying on teacher interviews, teachers complete a questionnaire, and parents complete a brief survey. Teacher surveys inform the ex0 level. At the macro level, meeting minutes, environmental assessment, and CAB measures will be examined.

To maximize understanding of the efficacy of the SAP, information will be collected from all stakeholders. CAB members will complete a survey evaluating their role with the collaboration. Teachers will complete self-evaluations of their ability to implement SAGE, score parent-teacher interactions that may affect sustainability, rate their self-efficacy for sustaining SAGE beyond the funding period, provide reflections on SAGE implementation after each session that are recorded in field notes, and participate in post-intervention interviews. ECEC will directors evaluate factors associated with program sustainability related to ECEC administration, policies, and procedures, rate how SAGE has impacted their site, score their self-efficacy for sustaining SAGE beyond the funding period, and participate in post-intervention interviews. Parents will complete surveys evaluating the newsletters and rating their interaction [33]. SAGE staff, in coordination with ECEC teachers and directors, will complete assessments to evaluate the physical activity and nutrition environment at the ECEC, as well as record meeting minutes of all meetings with CAB members, ECEC teachers, and ECEC directors. The timing of each assessment is presented in Table 2.

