### 2.10. Environmental Assessments

Three validated *Nutrition and Physical Activity Self-Assessment for Child Care (NAP SACC)* [46] environmental assessments at each ECEC will be used to measure the quality of resources related to physical activity, nutrition, and screen time. Evaluations used a combination of direct observation by research staff, self-report by teachers, and self-report by directors to measure outcomes. About two weeks before the start of the programming (either SAGE Garden or Child Safety), a research team member assesses outdoor play environment quality, ECEC teachers reported on the indoor environment, and the ECEC director reported the quality of physical activity, nutrition, and screen time policies. This 24-item assessment consists of check all that apply and Likert-type scale questions. For a further description of the assessment process, see Szeszulski et al., 2022 [47]. Responses from baseline to post-intervention will be compared to evaluate the impact of the SAP and SAGE on physical activity, nutrition, and screen time environments.

The *Physical Activity Resource Assessment (PARA)* is an established direct observation checklist [48] that is completed by SAGE staff on site at each ECEC two to three weeks before the start of programming. This assessment consists of fill in the blank, multiple choice, yes or no, and Likert-type scale questions. Questions focus on the availability of physical activity features such as sports fields, play equipment, and trails, amenities such as water fountains, lighting, and shade, and incivilities such as broken glass, graffiti, and vandalism. This 45-item assessment takes about 10 min to complete. Responses from baseline to post-intervention will be compared to evaluate the impact of the SAP and SAGE on the physical activity environment.

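### The staff-observed environment measures (PARA and outdoor NAP SACC) are rated by the project team that delivers SAGE, and the rating rule does not separate rater from deliverer

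*Protocol article*

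**What the plan says.** All references are to the protocol article. In it, SAP means the Sustainability Action Plan.

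**Who rates.** Section 2.4 covers the environment assessments in one sentence: "SAGE staff, in coordination with ECEC teachers and directors, will complete assessments to evaluate the physical activity and nutrition environment at the ECEC". Section 2.10 is more specific.
- The PARA "is an established direct observation checklist", and one "that is completed by SAGE staff on site at each ECEC two to three weeks before the start of programming".
- NAP SACC has mixed sources: "Evaluations used a combination of direct observation by research staff, self-report by teachers, and self-report by directors to measure outcomes". The parts are then assigned: "a research team member assesses outdoor play environment quality, ECEC teachers reported on the indoor environment". Policies are left to the director's own report.

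**How the ratings are used.** Section 2.10 compares baseline with post-intervention on both tools to evaluate the impact of the SAP and SAGE. Table 1 lists both under micro-level institutionalization, and NAP SACC is the only entry for macro-level institutionalization. The Discussion presents the plan as drawing on observed as well as self-reported data.

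**Who delivers.** Section 2.1: "CAB members, teachers, and SAGE staff work together to build the garden". Section 2.2: "The first 12 sessions will be led by the research team over six weeks, with teachers observing and assisting in SAGE delivery". Teachers lead the second six weeks with the research team assisting. Section 2.3 has SAGE staff bring supplies and give the initial training. Sections 2.2 and 2.3 have project staff meet directors to go through assessment results and set improvement goals.

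**The concern.** PARA and the outdoor NAP SACC are the part of the environment battery that does not come from the teachers' or directors' own reports. Their value depends on the observer having no part in what is being observed. Here the stated observers belong to the team that brings the programme to the centre, and the rating rule does not keep the person who rates a centre apart from those who build, train, lead sessions or coach there.

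Some items leave room for judgement. The outdoor NAP SACC rates quality, and the PARA includes Likert-type items. A rater who has worked at a centre for weeks may score it more favourably afterwards without meaning to. That would look like a programme effect.

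The section 2.4 wording adds a smaller problem. Read literally, it could bring teachers and directors into the observed ratings, although they already supply the self-reported parts.

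**Working it through.** The article gives no figure for rater agreement or bias, so apart from one count the check compares sections.

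**1. Share of sessions led by the team.** Section 2.2 plans two sessions a week for 12 weeks: 2 × 12 = 24. The research team leads the first 12: 12 / 24 = 50%. It assists in the other 12.

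**2. Roles side by side.**

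| Task | Who, as stated | Section |
|---|---|---|
| Build the garden | SAGE staff, with board members and teachers | 2.1 |
| Initial teacher training | SAGE staff | 2.3, step 1 |
| Lead sessions 1 to 12 | Research team | 2.2 |
| Assist sessions 13 to 24 | Research team | 2.2 |
| Review results and set goals with the centre | Research or SAGE staff | 2.2; 2.3, step 4 |
| Complete the PARA | SAGE staff | 2.10 |
| Rate the outdoor NAP SACC | A research team member | 2.10 |
| Report the indoor NAP SACC | Teachers | 2.10 |
| Report NAP SACC policies | Director | 2.10 |

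Delivery and observed rating fall to the same project team. The labels are group labels, so the overlap is shown for the team and not for named roles at a given centre.

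**3. Where a bias would enter.** For one centre:

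rated change = true change + (rater shift at post-intervention − rater shift at baseline)

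A rater who is equally lenient at both visits cancels out. A rater whose view becomes more favourable between the visits does not, and delivering the programme between them could have that effect. If the shift is similar across centres, averaging over more of them leaves it in place. In a comparison with the Child Safety programme, what remains is the difference between the two programmes' shifts. The article does not say who delivers Child Safety, so that remainder cannot be stated.

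**4. Sections 2.4 and 2.10 compared.** Section 2.10 divides NAP SACC among staff, teachers and director, and mentions no centre-staff input to the PARA. The natural reading of section 2.4 is that it summarizes this division. Its wording nevertheless covers the whole environment battery, including the observed items.

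**5. Could the rater be blinded?** The PARA is done two to three weeks before programming (section 2.10). The self-efficacy form is given at the teacher training, also two to three weeks before the start (section 2.7), and that training includes a garden tour with planting (section 2.3, step 1). A garden may therefore be in view at the baseline rating as well as afterwards. Blinding cannot be relied on at either visit.

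**The case against.** **Silence is not a fault.** The article condenses fuller material and refers elsewhere for more on the assessment process, so the absence of any word on blinding or rater assignment is no finding. That stands. The point here rests on what the article does state: it names SAGE or research staff as raters, and the same team as deliverers.

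**Overlap of individuals is not stated.** This also stands. A reader might infer that the person who led the sessions rates the centre. The text neither says so nor rules it out.

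**Sections 2.4 and 2.10 do not contradict each other.** A reader might infer that the observed ratings are agreed with teachers and directors, and so cannot serve as a check on the self-reports. The documents do not support this. Nowhere are centre staff said to see, discuss or agree those scores before they are recorded, and section 2.10 gives a benign meaning to the coordination phrase. What remains is a phrase wider than it needs to be.

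**Much of the PARA is factual.** Features, amenities and incivilities are largely matters of presence or count, and the example goals in section 2.3 are policies, funding and staff training. This limits the scope for bias, but it does not remove the Likert-type items or the outdoor quality rating.

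**Effect on the comparison with Child Safety.** A reader might infer that expectancy acts only at SAGE centres. The article does not support that, since it does not say who delivers Child Safety.

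**Conclusion.** The point holds in a limited form. The observed environment ratings are used as evidence of impact and come from the team that delivers the programme, with no separation of rater from deliverer in the rule as written. The items that need judgement are therefore open to expectancy bias.

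The size is unknown. The article gives nothing from which to estimate it, and any standard-deviation figure would only restate an assumption. What can be said is that a shift in rater leniency between the two visits passes in full into that centre's rated change, and that more centres would not remove a common shift.

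The conclusion rests on two assumptions: that the team labels in sections 2.1 to 2.4 and 2.10 refer to overlapping staff, and that some items are judged rather than counted. The self-reported NAP SACC parts are openly self-report and are outside this point. It is a worthwhile correction to the method, and does not make the environment data unusable.

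**What to change.** - **Separate the roles.** State in section 2.10 that a centre's PARA and outdoor NAP SACC are rated by an existing team member who does not deliver, train or coach at that centre, by swapping raters between centres.
- **Fix the order.** Record the ratings before any discussion of them with teachers or directors.
- **Narrow section 2.4.** Limit the coordination phrase to the self-reported NAP SACC parts.
- **Claim no more than this gives.** Describe it as rater independence, not blinding.
- **Report exceptions.** Where staffing does not allow a swap, report that the rater also delivered at that centre.

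The text changes are a few sentences. The rating work does not grow: the PARA takes about 10 minutes whoever completes it. The cost is some added scheduling and travel. The article gives no staffing numbers, so whether every centre can be covered by a swap is not known.
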